### Design plan

To assess the hypotheses, we will conduct a single-blind (online) experiment; participants will not know to which condition they were assigned but researchers will be aware of the respective treatments when analyzing the data. We will apply a between-subjects design that includes two factors (i.e., target group x descriptor) with two levels respectively (target group: people who have a physical disability, people who have committed a violent crime; descriptor: identity-first, person-first) as well as a control group. Simple randomization will be implemented to assign participants.

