#### Sample size

We aim to recruit *N* = 681 participants. The sample size calculation is based on an a-priori power analysis, considering the smallest effect of interest as a reference [47]. Our goal is to obtain .95 power, with α = .01 (Bonferroni-corrected p-value for five outcomes; see below), to be able to detect also small effects (or differences) of f = .175 with univariate analyses of variance (one-way). We will only recruit participants who are UK residents and older than 18 years. We introduce the former selection criterion (i.e., being a UK resident) as we will apply definitions of disability and violent crime (see Manipulated variables–experimental stimuli) that are provided by UK institutions.

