### Variables

#### Manipulated variables–experimental stimuli

In line with previous research [11, 12], the experimental conditions (and the control condition) will be defined by referring to (one of) five different groups when presenting the outcome measures (Table 1). That is, participants will complete outcome measures considering either ‘most people’ (control group), ‘violent criminals’ (identity-first language), ‘people who have committed a violent crime’ (person-first language), ‘the physically disabled’ (identity-first language), or ‘people who have a physical disability ‘ (person-first language).

**Table 1 pone.0300879.t001:** Instructions and group definitions.

Condition	Instructions and definition
Control group	To what extent do you agree with the following statements about most people?
negative attitudes are expected to be more important, identity-first language	To what extent do you agree with the following statements about violent criminals?
	Definition of a violent crime: harmful force is used upon a victim, with or without using a weapon, ranging from common assault to murder (CPS, 2023)
negative attitudes are expected to be more important, person-first language	To what extent do you agree with the following statements about people who have committed a violent crime?
	Definition of a violent crime: harmful force is used upon a victim, with or without using a weapon, ranging from common assault to murder (CPS, 2023)
negative attitudes are expected to be less important, identity-first language	To what extent do you agree with the following statements about the physically disabled?
	Definition of physical disability: a physical impairment that has a ‘substantial’ and ‘long-term’ negative effect on the ability to do normal daily activities (UK Equality Act 2010)
negative attitudes are expected to be less important, person-first language	To what extent do you agree with the following statements about people with a physical disability?
	Definition of physical disability: a physical impairment that has a ‘substantial’ and ‘long-term’ negative effect on the ability to do normal daily activities (UK Equality Act 2010)

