### Analysis plan

#### Data exclusion

We will exclude data from all participants who did not fully complete the study, failed either the attention or the manipulation check, or who indicated that they themselves had ever committed a violent crime or describe themselves as a person with a physical disability.

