#### Confirmatory analyses

We will test for median absolute deviation to detect potential univariate outliers for all outcome variables [49]. We do not plan to exclude outliers but will report their presence. Mean scores and standard variations of as well as bi-variate correlations between all measures will be calculated.

Examining Hypothesis 1a-e (i.e., the effects of person-first language), we will test the assumptions for univariate analysis of variances (ANOVA) for all five outcome measures separately for each of the two descriptor pairings (see Huang [50] who suggests multiple ANOVAs with p-values that are corrected for multiple comparisons rather than a multivariate analysis of variance). Once assumption checks confirmed the suitability of the tests, we will conduct five two-tailed ANOVAs, comparing the indices of positive and negative stereotyping, dehumanization, negative affect, and approach behavior intentions between the identity-first, person-first, and control condition regarding the descriptor pairing “people with a physical disability/the physically disabled”. The analyses will then be repeated for the descriptor pairing “people who have committed a violent crime/violent criminals”. Planned contrasts will be used to investigate for each descriptor pairing whether average negative outgroup perceptions and affect are lower, positive perceptions and approach behavior intentions are higher in the person-first as compared to the identity-first language condition. It is further expected that negative outgroup perceptions and affect are lowest as well as positive perceptions and approach behavior intentions are highest in the control condition. Effect sizes and confidence intervals will be computed. To correct for the multiple ANOVAs in each descriptor pairing, p-values are adjusted using the Bonferroni correction. We address concerns about the reduced power of the tests by using the corrected p-value of p = .01 (i.e., .05 divided by five) in the a-priori power analysis (see above).

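### The 681 participants match the requirement of a single three-group ANOVA, but they are spread over five arms, so each planned ANOVA has about 409 people and power of about .74, not .95

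*Protocol article*

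**What the plan says.** The Sample size section of the protocol article gives the total, "We aim to recruit *N* = 681 participants", and the target: "Our goal is to obtain .95 power, with α = .01 (Bonferroni-corrected p-value for five outcomes; see below"). The stated aim is "to be able to detect also small effects (or differences) of f = .175 with univariate analyses of variance (one-way"). The number of groups in the power analysis is not given. The Abstract attaches the same N to the whole experiment.

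The Design plan states: "We will apply a between-subjects design that includes two factors", each with two levels, plus a control group, with simple randomisation. Under Manipulated variables, the conditions "will be defined by referring to (one of) five different groups when presenting the outcome measures". Each participant therefore belongs to one of five arms.

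Under Confirmatory analyses, each outcome is compared "between the identity-first, person-first, and control condition regarding the descriptor pairing" for physical disability, and the five ANOVAs are then repeated for violent crime. The same section says the concern about lost power is met because the corrected α of .01 went into the sample-size calculation.

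Under Data exclusion: "We will exclude data from all participants who did not fully complete the study". Failed attention or manipulation checks, a self-reported violent crime and a self-described physical disability are also grounds for exclusion.

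**The concern.** The sample-size calculation and the analysis count people differently. A power of .95 for a three-group ANOVA on 681 people requires all 681 to be in that ANOVA. Each planned ANOVA leaves out the two arms of the other descriptor pairing, so no allocation that fills all five arms can put 681 people into either one.

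This is a stage-1 registered report, in which power at the smallest effect of interest is a commitment made before data collection. If the figure is wrong, a non-significant result on Hypotheses 1a–1e would be read as coming from a test with a 5% chance of missing an effect of f = .175, when the chance is about 26% or more. The error concerns sensitivity only: it does not bias the estimates or inflate the type I error.

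**Working it through.** **Inputs from the document.** Total N = 681, α = .05/5 = .01, target power .95 and f = .175 (Sample size); five between-subjects arms (Design plan, Manipulated variables); three arms per ANOVA (Confirmatory analyses).

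**Assumption.** Equal allocation. The document says simple randomisation and gives no ratio.

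**Formula.** For a one-way ANOVA with k groups, power = P(F′ > F crit), where F crit is the 1 − α quantile of F with k − 1 and N − k degrees of freedom, and F′ is noncentral F with noncentrality λ = N f².

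**Step 1: reproduce the plan's figure.** N for .95 power at α = .01 and f = .175:

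| Groups | Smallest N | Rounded up to equal groups | Power at N = 681 |
|---|---|---|---|
| 2 | 586 | 586 | .976 |
| 3 | 679 | **681** | **.951** |
| 4 | 747 | 748 | .925 |
| 5 | 802 | 805 | .898 |
| 6 | 849 | 852 | .872 |

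Only three groups gives 681 (3 × 227; λ = 681 × .175² = 20.86).

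**Step 2: count the people in each planned ANOVA.** 681 / 5 = 136.2 per arm; 681 × 3/5 = 408.6, about 409 per ANOVA.

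**Step 3: power of each planned ANOVA.** λ = 409 × .175² = 12.53 with 2 and 406 degrees of freedom; F crit = 4.66; power = .739. Type II error = 1 − .739 = .261.

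**Step 4: effect detectable with .95 power at N = 409.** Solving for f gives .226 (λ = 409 × .226² = 20.9).

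**Step 5: effect of exclusions.** The rates below are assumptions; the document gives none.

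| Excluded | Left per ANOVA | Power |
|---|---|---|
| 0% | 409 | .74 |
| 10% | 368 | .68 |
| 20% | 327 | .61 |
| 30% | 286 | .53 |

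**Step 6: N needed to keep .95.** 227 per arm × 5 arms = 1,135 analysable participants.

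**The case against.** **The number of groups is never stated.** True: that three groups lie behind 681 is inferred from the exact match. The conclusion does not need the inference. Whatever produced 681, the planned tests use three of five arms. A five-group ANOVA on all 681 is not the planned analysis and would also fall short, at .898.

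**Allocation might not be equal.** Equal shares are the natural reading of simple randomisation, but they are an assumption. If one third (227) were in the shared control, each ANOVA would have 227 + (681 − 227)/2 = 454 people and power of about .80. That narrows the gap but does not close it.

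**Exclusions may be handled elsewhere.** A condensed article may leave an attrition allowance, or replacement of excluded panel members, to other material. This is fair, and the exclusion figures are secondary. The .74 assumes no exclusions at all.

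**The omnibus F does not itself test Hypothesis 1.** This stands and limits what .74 means. Hypothesis 1 rests on the contrast of person-first with identity-first, and its power at f = .175 depends on the pattern of the three means. With 136 per arm and two-sided α = .01 (assumed for the contrast), noncentral t with noncentrality d√(136/2) and 405 degrees of freedom gives:

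- .21 if the means are equally spaced with person-first in the middle (d = .214). The Confirmatory analyses section expects that order; the spacing is assumed.
- .68 if person-first equals control (d = .371).
- .83 if control lies midway between the two descriptors (d = .429).

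The 1,135 likewise restores .95 only for the omnibus test. With 227 per arm the same contrast has power of .38, .91 and .98.

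**Effect sizes and confidence intervals will be reported.** They would show the imprecision to a careful reader, but they do not make the stated power correct.

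**Conclusion.** The point holds. The stated .95 power at f = .175 and α = .01 is not a property of any ANOVA in the plan. Under equal allocation and with no exclusions, omnibus power is about .74, a shortfall of about 21 percentage points, and the effect detectable with .95 power is f = .226 rather than .175. Nothing in the document says that 681 applies per pairing. The assurance under Confirmatory analyses that using the corrected α resolves the power concern fails for the same reason: the right α was paired with the wrong number of people. This must be corrected before data collection.

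**What to change.** Rewrite the Sample size paragraph to state:

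- the number of groups assumed in the power analysis and the allocation ratio;
- 681 recruited, about 136 per arm and about 409 per ANOVA;
- power of about .74 for the omnibus F at f = .175 and α = .01, or equivalently .95 power at f = .226;
- the same figure after the exclusion rate the investigators expect, or a statement that excluded participants will be replaced;
- that these figures concern the omnibus test, with power for the person-first versus identity-first contrast given separately under a stated pattern of means.

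Replace the sentence under Confirmatory analyses claiming that the power concern has been addressed.

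This costs text only and no extra participants, but it does give up the stated .95 goal at the smallest effect of interest, which the investigators must accept knowingly. If they want to keep .95 for the omnibus test at f = .175, the alternative is 1,135 analysable participants plus an allowance for exclusions: 1,135 − 681 = 454 more than now planned, even before that allowance. The document reports that no data have been collected, so either course is open.

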### Variables

#### Manipulated variables–experimental stimuli

In line with previous research [11, 12], the experimental conditions (and the control condition) will be defined by referring to (one of) five different groups when presenting the outcome measures (Table 1). That is, participants will complete outcome measures considering either ‘most people’ (control group), ‘violent criminals’ (identity-first language), ‘people who have committed a violent crime’ (person-first language), ‘the physically disabled’ (identity-first language), or ‘people who have a physical disability ‘ (person-first language).

**Table 1 pone.0300879.t001:** Instructions and group definitions.

Condition	Instructions and definition
Control group	To what extent do you agree with the following statements about most people?
negative attitudes are expected to be more important, identity-first language	To what extent do you agree with the following statements about violent criminals?
	Definition of a violent crime: harmful force is used upon a victim, with or without using a weapon, ranging from common assault to murder (CPS, 2023)
negative attitudes are expected to be more important, person-first language	To what extent do you agree with the following statements about people who have committed a violent crime?
	Definition of a violent crime: harmful force is used upon a victim, with or without using a weapon, ranging from common assault to murder (CPS, 2023)
negative attitudes are expected to be less important, identity-first language	To what extent do you agree with the following statements about the physically disabled?
	Definition of physical disability: a physical impairment that has a ‘substantial’ and ‘long-term’ negative effect on the ability to do normal daily activities (UK Equality Act 2010)
negative attitudes are expected to be less important, person-first language	To what extent do you agree with the following statements about people with a physical disability?
	Definition of physical disability: a physical impairment that has a ‘substantial’ and ‘long-term’ negative effect on the ability to do normal daily activities (UK Equality Act 2010)

#### Measured variables

Unless indicated otherwise, all measures mentioned below will apply a 5-point Likert-type scale (1 = ‘not at all’, 3 = ‘neither agree nor disagree’, 5 = ‘completely’).

*Attitude importance* will be measured in a pre-test. Attitude importance is commonly assessed by asking participants how concerned they are about a specific issue, rather than how much they care about their attitudes on this issue; both approaches have been found to be valid [15]. Participants will be presented with a list of five topics (i.e., two target and three filler topics: violent crime, taxes, physical disability, climate change, and product placement in movies) and asked to indicate their opinion about the topics (i.e., valence; 1 = very negative, 7 = very positive) as well as how important these topics are for them (1 = not at all important, 5 = very important). That is, in the pre-test, we make references neither to person- nor identity-first language.

In the main study, and after providing participants with a definition of either the term physical disability or violent crime (Table 1), we will rely on an adapted version of Enock and Over’s [48] scales that explore desirable and undesirable outgroup traits that are either uniquely human (i.e., two positive and two negative stereotypes: knowledgeable, open-minded, arrogant, controlling) or traits that humans share with animals (i.e., dehumanization: calm, curious, inflexible, unsophisticated). In doing so, we distinguish stereotyping from dehumanization [48]. Negative affect will be measured with three items (‘I would be afraid to be around ….’, ‘I would be upset if … moved into my neighbourhood’, ‘I feel disgusted by …’). Outgroup approach behavior intentions will examine willingness for intergroup contact in different settings (‘I would not want to work with …’, ‘I would not want to live near …’, ‘I would want to be friends with …’, ‘I would never be willing to date …’).

An attention check will be embedded in the list of aforementioned items (‘This is an attention check. Please answer ’Not at all’ to indicate that you pay attention.’). Lastly, participants will be asked to complete a manipulation check (‘You have just answered several questions about a specific group of people. How was this group referred to?’ Answer options: Violent criminals, People with a physical disability, Most people, The physically disabled, People who have committed a violent crime, My friends) and indicate whether they themselves have ever committed a violent crime (No/Yes) or describe themselves as a person with a physical disability (No/Yes).

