#### Indices

The following indices will be created by calculating mean scores: positive and negative traits that are uniquely human (positive and negative stereotypes; two items each) or shared with animals (dehumanization; four items); negative affect (three items); as well as willingness for intergroup contact (four items).

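### The default outcome scale joins amount-type end points to a disagree-agree midpoint, which may add measurement error of unknown, possibly nil, size (minor)

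*Protocol article*

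**What the plan says.** Measured variables states that, unless indicated otherwise, "all measures mentioned below will apply a 5-point Likert-type scale", with anchors "1 = ‘not at all’, 3 = ‘neither agree nor disagree’, 5 = ‘completely". Labels for points 2 and 4 are not given. Only the pre-test items have their own anchors: valence on a 1 to 7 scale, and importance as "how important these topics are for them (1 = not at all important, 5 = very important". The default therefore governs all five outcome indices.

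Table 1 gives the stem, which has the same form in all five conditions. For the control group it reads "To what extent do you agree with the following statements about most people". The attention check tells participants to choose the 'not at all' option, so that anchor is on the fielded form and is not a shorthand of the article.

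Under Indices: "The following indices will be created by calculating mean scores". Positive and negative stereotypes have two items each, negative affect three, dehumanization four and approach intentions four.

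**The concern.** Under a stem that asks how far one agrees, 'not at all' means zero agreement and 'completely' means full agreement. That is a one-sided amount scale, whose middle should be a moderate amount of agreement. The printed middle is instead the neutral point of a two-sided scale, with no labelled disagree end to balance it.

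Someone with no view on whether a group is, say, arrogant does not agree at all, which points to 1, and neither agrees nor disagrees, which is printed at 3. Someone who half agrees finds the middle labelled as neutrality. If participants resolve this differently, the same attitude receives different scores. Such a reading habit belongs to the person and can repeat across items. What is at stake is extra noise, and so lower sensitivity, in the person-first versus identity-first contrasts.

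**Working it through.** **1. The plan's own figure.** Sample size states "We aim to recruit *N* = 681 participants", with "Our goal is to obtain .95 power, with α = .01", for "small effects (or differences) of f = .175 with univariate analyses of variance (one-way". For a one-way ANOVA with k groups, power is P(F′ > F crit), where F′ is noncentral F with k − 1 and N − k degrees of freedom and noncentrality λ = N·f². With k = 3, f = .175 and α = .01, N = 679 is the smallest total that reaches .95. Rounded up to equal groups this is 681 (227 each), with power .951. The figure reproduces as a three-group ANOVA. Because f is a standardised input, N does not depend on the anchors.

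**2. What one neutral person scores.** Compare a respondent who is neutral on every item and marks 3 with one who marks 1. For mixed indices, reverse-scoring (6 minus the answer) is assumed; the article does not spell it out.

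| Index | Item directions | Marks 3 | Marks 1 | Shift |
|---|---|---|---|---|
| Positive or negative stereotypes | 2 same | 3 | 1 | −2 |
| Negative affect | 3 same | 3 | (1+1+1)/3 = 1 | −2 |
| Approach intentions | 3 reversed, 1 not | 3 | (5+5+5+1)/4 = 4 | +1 |
| Dehumanization | 2 and 2 | 3 | (1+1+5+5)/4 = 3 | 0 |

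The three same-direction indices carry the full shift. Approach intentions carry half of it, and for dehumanization it cancels.

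**3. Illustrative effect on the standardised difference.** The documents give neither a misreading share nor a response distribution, so everything here except α, f and N is assumed:
- Latent d = 2f = 2 × .175 = .35 on the index.
- Normal latent items with inter-item correlation .5, cut at −1.5, −.5, .5 and 1.5.
- A share q of participants marks 1 wherever they would otherwise mark 3; all other answers are unchanged.
- q is the same in both arms.
- Observed d = difference in index means ÷ pooled SD.

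| Index | q = 0 | 10% | 25% | 50% |
|---|---|---|---|---|
| Three same-direction items, mid-scale targets | .34 | .32 | .30 | .28 |
| Same, targets one latent SD lower | .34 | .32 | .29 | .26 |
| Four items, 2 and 2, reverse-scored, mid-scale | .34 | .33 | .33 | .32 |
| Four items, 3 and 1, reverse-scored, mid-scale | .35 | .34 | .32 | .31 |

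Simulation error is under about .01. In the first row the loss relative to q = 0 is .02/.34 ≈ 6%, .04/.34 ≈ 12% and .06/.34 ≈ 18%.

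**4. In power terms.** Equal allocation is assumed, so 681/5 ≈ 136 per arm. For a two-sided contrast at α = .01 (noncentral t), the first row gives about .59, .52, .45 and .40. The starting value of .59 is not a scale effect. With no coarsening at all, d = .35 gives .62 at 136 per arm. Only the drop from .59 can be put down to the assumed misreading.

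**The case against.** The strongest reply is that the scale will be read by position. Five ordered points follow an agreement stem, the middle is explicitly labelled neutral, and a respondent without a view sees a point that says so. The lower end then serves as full disagreement, q is near zero and nothing is lost. The documents cannot rule this out, so the reply stands as a limit on the size of the problem. It does not make the anchors coherent.

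A reader might go further and infer any of the following. The documents do not support them.

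- *The person-first effect is attenuated, and with it the Hypothesis 2 bounds.* This needs a non-zero misreading share, and the protocol gives no information on that. It is a possibility, not a finding.
- *The loss is larger than shown.* A harsher model also moves 'disagree' answers to 1 and 'agree' answers to 3, which gives about .34/.31/.27/.26 in the first setting. It requires people who agree to tick a box that says they neither agree nor disagree, and it goes beyond the ambiguity about neutral views.
- *All five outcomes suffer alike because averaging cannot remove the shift.* That fails for the two mixed-direction indices if they are reverse-scored.
- *The comparison is biased.* All arms share the stem and scale and are randomised. Misreading adds noise or compresses scores, and it favours neither descriptor unless its rate depends on the descriptor, for which there is no evidence.

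**Conclusion.** The inconsistency is on the page and applies to every outcome: an amount-type floor and ceiling around a two-sided neutral midpoint, with no labelled disagree end. The supportable consequence is modest. It may add measurement error and reduce sensitivity, chiefly for negative affect and for positive and negative stereotypes, and less for dehumanization and approach intentions if these are reverse-scored.

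The size is unknown. Under the neutral-only assumption, with mid-scale targets and same-direction items, observed d falls from about .34 to .32, .30 or .28 at assumed shares of 10, 25 or 50%. It does not fall if respondents read by position. No bias between arms is expected, and the stated N is unaffected. This is a minor point, worth making because it is cheap to remove now and hard to correct once data are in, since the two kinds of reader cannot be told apart from their answers.

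**What to change.** Before fielding, use one coherent anchor set for all agreement items. The preferred set is 1 = strongly disagree, 2 = disagree, 3 = neither agree nor disagree, 4 = agree, 5 = strongly agree. If an amount scale is wanted, use 1 = not at all, 3 = moderately, 5 = completely, and drop the neutral label. Reword the answer that the attention check asks for, so that it exists on the chosen scale.

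The cost is label text in the Qualtrics form and one line of the protocol. Items, analysis and sample size stay as they are. No data have been collected, and the Timeline section already allows one week for requested changes. The one downside is a small loss of comparability with earlier uses of the same anchors, if there are any.
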